### Endpoints and statistical analyses

The primary outcome measures are safety and tolerability as measured by treatment-emergent adverse events.

The secondary objectives for efficacy are changes in outcome variables, from the baseline/run-in period (12 weeks) before intervention, and through 40 weeks follow-up from start of intervention for SF36 domains including SF36 Physical Function (SF36-PF) and SF36 Bodily pain (SF36-BP), DSQ-SF, Self-reported Function level, and Steps per 24 hours.

The pilot study is explorative, with no blinding or placebo group. We will not describe patients dichotomously as responders or non-responders. Rather, the outcome measures will be descriptive, and assessed by changes in the courses of variables from baseline through 52 weeks from inclusion, including a 12-week run-in before intervention, and 40 weeks after start of intervention. For patients receiving additional maintenance injections at weeks 26, 34 and 42, the analyses will be extended through follow-up to week 72. The outcome variables for efficacy will be assessed by General Linear Model (GLM) Repeated measures for time effects, with the baseline values given as mean values for the 12 week run-in period before start of intervention.

We will also perform analyses for changes in outcome measures at fixed time points compared to baseline, at end of run-in period (i.e. at 12 weeks) and again at 16, 18, 20, 22, 24, 28, 32, 40, 48 and 52 weeks, for patients receiving additional maintenance injections extended at four-week intervals to week 72. Differences in outcome measures from baseline, and from end of run-in at 12 weeks, to the fixed time points after intervention will be assessed by paired t-test or by Wilcoxon paired non-parametric tests.

Extended follow-up may be performed also after end of study, either by clinic attendance or by telephone, to monitor any toxicity or ongoing clinical responses.

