## **A pilot study of 10 patients with moderate to severe ME/CFS, using four subcutaneous injections of the anti-CD38 antibody daratumumab, with follow-up for 12 months (KTS-9-2022)**

### **Purpose**

The main purpose is to evaluate feasibility and safety of daratumumab subcutaneous injections in patients with moderate to severe ME/CFS. We will also collect efficacy data.

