### **Design**

An exploratory pilot study of six patients with moderate to severe ME/CFS. After inclusion, there will be an initial 12-weeks observational run-in period, followed by administration of 4 subcutaneous injections of the anti-CD38 antibody daratumumab with 2-week intervals. Patients will be subject to clinical follow-up for 40 weeks from start of intervention. Four additional patients will receive the same intervention, and if they show improvement of ME/CFS symptoms by clinical evaluation six weeks after the fourth injection (at study week 24), they will receive three additional maintenance daratumumab injections at weeks 26, 34 and 42.

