### Daratumumab intervention

After 12 weeks’ run-in, patients will start intervention.

The first two patients will receive two subcutaneous injections of daratumumab two weeks apart, followed by an observation period of four to six weeks. If there is no serious, unexpected toxicity, we will proceed with another two injections two weeks apart.

After these two patients have received the planned four daratumumab subcutaneous injections, the Safety board will review the data.

Subject to a favorable Safety board review, the pilot study will proceed with the four remaining patients, who will receive four subcutaneous injections of daratumumab two weeks apart.

Thus, all patients will receive in total four subcutaneous injections of daratumumab.

According to a second amendment to the protocol, among four additional patients included, provided clinical improvement at week 24, these will receive additional three daratumumab injections, at weeks 26, 34 and 42, and with extended follow-up until week 72.

The injections will be administered in the outpatient clinic in the Department of Oncology and Medical Physics at Haukeland University Hospital.

Oral premedication will be given at least one hour before daratumumab injection. Before the first daratumumab injection: Dexamethasone 10 mg orally, Cetirizine 10 mg orally, Paracetamol 1 g orally, Montelukast 10 mg orally. Also, at least 20 minutes before daratumumab: Dexchlorpheniramine 5 mg iv.

On the following two days (2 and 3): Dexamethasone 4 mg orally.

Before the second and subsequent daratumumab injections, if no reaction to the first injection: Dexamethasone 10 mg orally, Cetirizine 10 mg orally, Paracetamol 1 g orally.

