Memory B-cells do not express significant amounts of CD38, and re-emergence of antibodies over time would be expected. According to our pathomechanistic hypothesis (13), with autoantibodies emerging after infection which persist and target blood vessel flow regulation, we believe that the ME/CFS disease is a reversible disease. We acknowledge that patients may also experience spontaneous remissions. We do not know if and when the putative autoantibodies will reappear after daratumumab intervention, but it is conceivable that a “resetting” of the plasma cell compartment could induce a sustained remission in some patients.

In this pilot study, we have in the original protocol not included any maintenance treatment to prolong possible clinical responses. We anticipate that four administrations of standard daratumumab dosing in each injection will be sufficient to assess feasibility and toxicity, and also to give indications for possible clinical benefit.

Based on observations of patients in the pilot study until March 2023, according to a second amendment, four additional patients will be included in the pilot study. For these four new patients, if clinically assessed improvement of ME/CFS symptoms at week 24, these will receive three additional daratumumab injections 8 weeks apart, i.e. at weeks 26, 34 and 42, and with prolonged follow-up until week 72.

A possible future larger study could verify or refute such efficacy, and if we observe clinical responses with limited duration after daratumumab, possible options include a prolonged daratumumab induction treatment or inclusion of a maintenance phase using e.g. B-cell depletion with rituximab, or anti-BAFF antibody treatment with belimumab.

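### Efficacy after week 26 is not separated by cohort or regimen, and the week 56–72 tests cover at most four patients chosen because they had improved

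*Protocol*

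**What the plan says.** The study heading in the protocol reads "A pilot study of 10 patients with moderate to severe ME/CFS". Design opens with "An exploratory pilot study of six patients with moderate to severe ME/CFS", who receive four injections after a 12-week run-in, and then adds four patients. Those four are to receive three further injections at weeks 26, 34 and 42 on one condition: "if they show improvement of ME/CFS symptoms by clinical evaluation six weeks after the fourth injection (at study week 24". Daratumumab dosing and administration introduces the added cohort with the words "Based on observations of patients in the pilot study until March 2023".

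Endpoints and statistical analyses describes a single set of efficacy analyses:

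- a repeated-measures GLM for time effects through week 52, with the run-in mean as baseline;
- comparisons at weeks 16, 18, 20, 22, 24, 28, 32, 40, 48 and 52 against baseline and against week 12, which "will be assessed by paired t-test or by Wilcoxon paired non-parametric tests".

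No division by cohort or regimen is given. The section continues: "For patients receiving additional maintenance injections at weeks 26, 34 and 42, the analyses will be extended through follow-up to week 72", with fixed time points every four weeks. It also calls the study explorative and the outcome measures descriptive.

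Daratumumab intervention gives the first two patients a four-to-six-week observation period after their second injection. It states "Thus, all patients will receive in total four subcutaneous injections of daratumumab", and the next paragraph gives three more injections to some patients.

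**The concern.** A time effect estimated across all patients after week 26 would average over people who have stopped treatment and people still receiving it. It would describe neither course.

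The extension to week 72 has a different problem. Patients enter that analysis only if they were judged improved at week 24, and they are then tested for change from baseline on symptom measures related to that judgement. ME/CFS symptoms fluctuate, and the protocol itself acknowledges natural symptom variation and spontaneous remission. Selection on a good week-24 state therefore carries forward as apparent later benefit even if the drug does nothing. There is no control group to show this. Efforts to reduce risks says that the results may provide the rationale for a larger trial, so a misleading late curve could matter there.

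**Working it through.** The protocol states no power, significance level or detectable effect, so there is no figure of its own to reproduce. Two-sided 0.05 is assumed below.

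**Mixing of regimens.** Inputs: ten fixed weeks (Endpoints and statistical analyses); maintenance at weeks 26, 34 and 42 for at most 4 of 10 patients (Design).

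- Fixed weeks after week 26: 28, 32, 40, 48 and 52, which is 5 of 10.
- Injections received by a maintained patient: 4 + 1 = 5 at weeks 28 and 32; 4 + 2 = 6 at week 40; 4 + 3 = 7 at weeks 48 and 52. All others have had 4.
- Share of patients on maintenance, with k maintained: k/10 for k = 0 to 4, so 0 to 40%.

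**Smallest attainable Wilcoxon p.** For an exact two-sided signed-rank test without ties or zeros, the minimum is 2/2^n.

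| n | minimum p |
|---|---|
| 2 | 2/4 = 0.5 |
| 3 | 2/8 = 0.25 |
| 4 | 2/16 = 0.125 |
| 6 | 2/64 = 0.031 |
| 10 | 2/1024 = 0.002 |

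**Paired t-test.** It can reach 0.05 with four patients (critical value 3.18 on 3 degrees of freedom). For 80% power it needs a mean change of about 2.1 SD at n = 4 and 3.3 SD at n = 3.

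**Effect of selection with no drug effect.** Let the week-24 change and the later change be standard normal with correlation r, and select patients whose week-24 change is above zero. Then E[Z | Z > 0] = √(2/π) = 0.798, and the expected later change is r × 0.798.

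- r = 0.3: 0.3 × 0.798 = 0.24 SD.
- r = 0.5: 0.5 × 0.798 = 0.40 SD.
- r = 0.7: 0.7 × 0.798 = 0.56 SD.

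The protocol gives neither r nor a numerical cut-off, so both are assumptions. A simulation of 100,000 sets of four candidates gave the same means. When all four were selected, the t-test was significant in the favourable direction in 5.4%, 8.6% and 14.7% of runs at r = 0.3, 0.5 and 0.7, against a nominal 2.5%. Over groups of two to four the figures were 4.1%, 6.0% and 8.8%.

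**The case against.** The strongest reply has three parts. Efficacy is secondary and explicitly exploratory, and the protocol says that the small number prevents firm conclusions. Analysis sets are commonly defined in a statistical analysis plan, which is not at hand. And the section already names the maintenance patients as a group. The first part stands and limits the severity. The other two stand only partly, because the protocol itself prescribes the paired tests, sets no split through week 52 and carries the same analyses to week 72 for the selected patients.

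Some stronger readings are tempting but are not supported:

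- **The protocol explicitly pools all ten patients to week 52.** That is the plain reading of an undivided analysis, but the section does not say so in words.
- **Maintenance contradicts "We will not describe patients dichotomously as responders or non-responders".** That sentence concerns how outcomes are described. A decision to continue treatment is not an outcome description.
- **A clinical evaluation at week 24 conflicts with the telephone contact in the schedule.** The text does not require attendance in person, and SF-36, DSQ-SF, function level and HADS are all scheduled that week.
- **The cohort was expanded because early efficacy looked good, so pooled p-values are inflated by a calculable amount.** The protocol mentions observations but not that they were favourable, and it gives no expansion rule. Any figure would rest on an invented one.
- **No test in the maintenance group can reach significance.** This is true of the Wilcoxon test only.

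**Conclusion.** The point holds as a defect in the analysis wording that should be corrected, not as a threat to the primary safety objective. On the plain reading, half of the fixed time points after the first injection mix regimens, with up to 40% of patients on maintenance.

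The week 56–72 tests are uninformative by Wilcoxon (floor 0.125 at n = 4, 0.25 at n = 3) and tilted in the favourable direction by t-test. The tilt of about 0.24 to 0.56 SD holds in expectation only. It depends on a positive correlation between week-24 and later changes and on selection at any improvement. A reader might infer that a lasting response at week 72 would appear whatever the drug does. The calculation does not show that: without a drug effect the expected change shrinks from 0.80 SD at week 24 to 0.24–0.56 SD later, and individual results may go either way.

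**What to change.** In Endpoints and statistical analyses:

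1. After week 26, present efficacy separately for the original six and the additional four, marking which patients received maintenance, and treat any pooled estimate after week 24 as secondary. The split should be by cohort, because a patient's cohort does not depend on that patient's outcome. A split by maintenance received would itself be a split on improvement.
2. Replace the tests at weeks 56–72 with individual profiles, and state that these patients were selected on improvement at week 24.
3. Up to week 24, show each cohort beside any pooled estimate. Note that the second cohort was added after earlier patients had been observed, and that the first two patients had a longer gap after their second injection, so exposure already differs in weeks 16 to 24.

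In Daratumumab intervention, reconcile the statement that every patient receives four injections in total with the maintenance text that follows it.

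The cost is wording only, since all the data are already scheduled. The price is precision after week 26. For the same SD, the standard error grows by √(10/6) = 1.29 for the six and √(10/4) = 1.58 for the four. The change detectable with 80% power rises from about 1.0 SD with ten patients to about 1.4 SD with six.

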### Patient information and informed consent process

Candidates will be invited to attend the study centre for a consultation with one of the investigators. This initial visit can be replaced by a telephone consultation.

The candidates will receive a written patient information letter/declaration of consent and given ample time (a minimum of 24 hours) to consider before giving their written consent. No study specific analyses or tests will be performed prior to written informed consent.

Participants will also be requested to donate blood samples to the project biobank (2018/1532 «Disease mechanisms in ME/CFS»; [name] is responsible for the biobank, which is located at the Dept. of Oncology and Medical Physics at Haukeland University Hospital). A separate consent form will be signed before harvesting blood samples for the biobank.

## Assessment at baseline

### Clinical assessment

One of the investigators will assess the complete disease history for ME/CFS, previous diseases and comorbidity, perform a clinical examination, and will assess any need for further diagnostic evaluation.

The investigator will assess the severity grade of ME/CFS, and may include patients with either moderate (mainly housebound), moderate-to-severe, or severe (mainly bedridden) ME/CFS. The ME/CFS disease onset should be defined and preceded by either an infection or another immunologic stimulus.

If the clinical assessment uncovers other medical conditions which, according to the investigator's assessment, could be the cause of profound fatigue and post-exertional malaise, the patient will not be included.

Conditions that may be interpreted as a cause of persistent profound fatigue include hypothyroidism not adequately substituted with thyroxin, hypocortisolism, malignant disease, chronic infections, chronic pulmonary disease, renal failure, chronic liver disease, chronic heart disease, chronic neurologic disease, endogenous depression, other psychiatric conditions associated with fatigue.

### Women of childbearing potential

For women of childbearing potential, a serum pregnancy test at baseline must be negative. A woman is considered of childbearing potential (WOCBP), i.e. fertile, following menarche and until becoming post-menopausal unless permanently sterile. Permanent sterilization methods include hysterectomy, bilateral salpingectomy and bilateral oophorectomy.

A postmenopausal state is defined as no menses for 12 months without an alternative medical cause. Highly effective contraceptive measures include: combined (estrogen and progestogen containing) hormonal contraception associated with inhibition of ovulation; progestogen-only hormonal contraception associated with inhibition of ovulation, intrauterine device (IUD), intrauterine hormone-releasing system (IUS), bilateral tubal occlusion, vasectomized partner, sexual abstinence.

Women of childbearing potential must use effective contraceptive methods for at least 4 weeks before start of treatment and at least 24 weeks following the administration of the last daratumumab injection. A man who is sexually active with a woman of childbearing potential must use a barrier method of birth control for at least 4 weeks before start of treatment and for 24 weeks after intervention.

### Laboratory tests at baseline

Tests for immunology, endocrinology or serology are not required at baseline if they have been performed in the last 6 months.

### General laboratory tests

Hemoglobin, leucocytes with differential count, thrombocytes, ferritin, s-iron, s-iron binding capacity, transferrin receptor, cobalamin, folate, Na, K, Ca, Mg, phosphate, glucose, creatinine, urate, total cholesterol, HDL cholesterol, 25-hydroksy vitamin D, ALAT, ALP, GT, bilirubin, CRP, ESR, albumin, total protein, INR. s-HCG (test for pregnancy) for women of childbearing potential. Urine analysis (dipstick test).

### Immunology

Serum protein electrophoresis, Immunoglobulins IgG, IgG1, 2, 3, 4 subclasses, IgM, IgA. Lymphocyte subtypes in peripheral blood (CD19, CD3, CD4, CD8, CD56/16, ratio CD8/CD4). Antibodies to transglutaminase, antinuclear antibodies, anti-CCP, anti-thyroid- antibodies (anti-TPO), antibodies to cardiolipin. Vaccination status with titers of antibodies to tetanus, diphtheria, pertussis and Covid-19.

### Endocrinology

Free-T4, TSH, prolactin, cortisol/ACTH.

### Microbiology

Serology for EBV, CMV, Parvovirus B19, Borrelia, HIV, Hepatitis (HBV, HCV).

### Blood typing

Daratumumab binds to CD38 is present to some extent also on erythrocytes, which may cause a false positive indirect Coombs test for up to 6 months after the last infusion. Determination of ABO- and Rh-status will not be affected, while presence of antibodies in serum to weak antigens may be masked. Blood typing will therefore be performed before start of intervention. The patients will be instructed to carry a card in their wallet describing that they have received daratumumab, with information regarding possible blood transfusions, in case of an emergency.

### Biobank at baseline

Blood samples will be harvested for the biobank at baseline:

- 1 x 6 ml EDTA-Plasma
- 1 x 6 ml EDTA-Blood
- 3 x 10 ml Serum
- 2 x 9 ml Tempus Blood RNA

## Intervention

After information and signed consent, patients will be instructed on how to fill in the questionnaires at baseline and at intervals during follow-up. The pilot trial set-up is shown in Figure 2.

[figure not shown]

### “Run-in” period before intervention

To capture aspects of natural symptom variation over time, patients will receive no intervention during the first 12 weeks of the study, but they will complete questionnaires at 2-week intervals and use the Fitbit armbands for continuous registration of steps per 24 h, resting heart rate and heart rate variability.

### Inclusion period

There is limited experience for the use of daratumumab in non-malignant indications. The drug has shown a favorable toxicity profile in the reported small series of patients with diverse autoimmune conditions, as detailed in the project description.

However, daratumumab has not previously been used in ME/CFS. We will therefore start intervention initially in two patients and then wait for at least eight weeks (i.e. at least two weeks after the fourth and last injection) for observation and assessment of any unexpected adverse events, before proceeding to start intervention in the remaining four patients. The safety board of the study will review and assess safety data after the first two patients have completed intervention.

### Daratumumab intervention

After 12 weeks’ run-in, patients will start intervention.

The first two patients will receive two subcutaneous injections of daratumumab two weeks apart, followed by an observation period of four to six weeks. If there is no serious, unexpected toxicity, we will proceed with another two injections two weeks apart.

After these two patients have received the planned four daratumumab subcutaneous injections, the Safety board will review the data.

Subject to a favorable Safety board review, the pilot study will proceed with the four remaining patients, who will receive four subcutaneous injections of daratumumab two weeks apart.

Thus, all patients will receive in total four subcutaneous injections of daratumumab.

According to a second amendment to the protocol, among four additional patients included, provided clinical improvement at week 24, these will receive additional three daratumumab injections, at weeks 26, 34 and 42, and with extended follow-up until week 72.

The injections will be administered in the outpatient clinic in the Department of Oncology and Medical Physics at Haukeland University Hospital.

Oral premedication will be given at least one hour before daratumumab injection. Before the first daratumumab injection: Dexamethasone 10 mg orally, Cetirizine 10 mg orally, Paracetamol 1 g orally, Montelukast 10 mg orally. Also, at least 20 minutes before daratumumab: Dexchlorpheniramine 5 mg iv.

On the following two days (2 and 3): Dexamethasone 4 mg orally.

Before the second and subsequent daratumumab injections, if no reaction to the first injection: Dexamethasone 10 mg orally, Cetirizine 10 mg orally, Paracetamol 1 g orally.

#### **Daratumumab dosing, injection, and injection-related reactions (IRR)**

Daratumumab subcutaneous injections will be given at a fixed dose of 1800 mg. A 15 ml syringe, which also contains recombinant hyaluronidase, is injected over 3-5 minutes into the abdomen approximately 7-8 cm to the right or left of the umbilicus (rotating injection sites for successive injections), on intact, healthy skin.

The patient will stay in the outpatient ward for at least 6 hours after the first Daratumumab injection, for observation of any injection-related reactions (IRR). Intravenous access will be established before the injection for administration of premedication and will be maintained throughout the observation period. Any allergic reactions or IRR will be treated according to standard hospital procedure.

If no IRR after the first injection, the observation period following the subsequent three injections will be 2 hours.

IRR after subcutaneous injections occurred in 9% of patients with multiple myeloma after the first injection, usually of grade 1-2. The risk of IRR will probably be lower in these patients without malignant plasma cells due to the low number of CD38 positive plasma cells. In the small patient series using daratumumab in autoimmune diseases, IRR was not reported to be a clinical problem.

If a patient suffers a severe allergic reaction or injection-related reaction (grade 4), the patient will not receive further daratumumab intervention.

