### Efforts to reduce risks

Our research group, based in an oncology department, has access to the necessary treatment and laboratory facilities, and we have clinical experience with follow-up of ME/CFS patients as well as extensive experience with immunomodulatory drugs. We will make efforts to reduce the stress and burden for patients participating in the pilot study, with facilitation for treatment in the outpatient cancer ward. The patients will have direct access to the study management throughout the study period, and will also be able to contact the doctor on duty at the Dept. of Oncology, Haukeland University Hospital if and when necessary.

The participants will undergo regular clinical and laboratory assessments as outlined in the protocol. They will be observed in the outpatient clinic for 6 hours after the first injection, and at least 2 hours after the remaining 3 injections. They will receive pre-medication before daratumumab injections to minimize the possibility for injection-related reactions. Measures will be taken to prevent complications such as virus reactivation and interference with pre-transfusion screening, as outlined under *Intervention* and *Blood typing*.

The first two patients will receive two subcutaneous injections of daratumumab two weeks apart, followed by an observation period of four to six weeks. If there is no serious, unexpected toxicity, we will proceed with another two injections two weeks apart.

After these two patients have received the planned four injections of daratumumab, and before the remaining four patients start intervention, an independent Safety board will perform a formal assessment on safety.

We have since 2016 discussed the concept of plasma cell targeting using the monoclonal anti-CD38 antibody daratumumab ME/CFS, but have delayed an application because there has been limited published data on the use in non-malignant indications. However, the general

impression from recent studies using daratumumab in several autoimmune disease, is that the drug is well tolerated with a favorable toxicity profile, and with good efficacy in antibody-mediated diseases in which the autoantibodies are produced by long-lived plasma cells. There have been few infusion-related reactions, which are relatively often seen in multiple myeloma.

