### Adverse event/ serious adverse event

#### Definition of adverse events (AE)

An Adverse Event (AE) is any untoward medical occurrence in a patient administered a pharmaceutical product and which does not necessarily have to have a causal relationship with this treatment. It can therefore be any unfavorable and unintended sign, symptom, or disease temporally associated with the use of a medicinal product, whether or not considered related to the medicinal product. This includes any occurrence that is new in onset or aggravated in severity from the baseline condition, or abnormal results of any diagnostic procedures, including laboratory testing abnormalities.

All toxicity will be graded according to Common Terminology Criteria for Adverse Events (CTCAE) guidelines (version 5.0).

Adverse events will be graded using the following criteria:

- Grade 1 (Mild): discomfort noticed but no disruption of normal daily activity.
- Grade 2 (Moderate): discomfort sufficient to reduce or affect normal daily activity.
- Grade 3 (Severe): inability to work or perform normal daily activity.
- Grade 4 (Life-threatening or disabling): represents an immediate threat to life.

Furthermore, adverse events will be classified into serious adverse event (SAE) yes/no.

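### Premedication and observation step down on the result of injection 1 alone, so a first reaction at a later injection does not restore them

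*Protocol*

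**What the plan says.** Protocol, Daratumumab intervention. Before injection 1 the patient receives dexamethasone 10 mg, cetirizine 10 mg, paracetamol 1 g and montelukast 10 mg by mouth, and dexchlorpheniramine 5 mg intravenously. The text then adds: "On the following two days (2 and 3): Dexamethasone 4 mg orally". A shorter list (dexamethasone 10 mg, cetirizine 10 mg, paracetamol 1 g) applies as follows: "Before the second and subsequent daratumumab injections, if no reaction to the first injection".

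Protocol, Daratumumab dosing, injection, and injection-related reactions (IRR). The patient stays at least 6 hours after injection 1, and "Intravenous access will be established before the injection for administration of premedication and will be maintained throughout the observation period". For the next injections: "If no IRR after the first injection, the observation period following the subsequent three injections will be 2 hours". The same section reports first-injection reactions in 9% of myeloma patients, "usually of grade 1-2", and expects a lower risk here. Dosing stops after a severe allergic reaction or a grade 4 reaction.

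Protocol, Efforts to reduce risks, restates the later observation period without any condition: "and at least 2 hours after the remaining 3 injections".

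The second amendment added injections at weeks 26, 34 and 42 for those of the four additional patients who improve by week 24.

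**The concern.** The protocol treats a reaction to injection 1 as a reason not to relax precautions. It gives no reason why the same reaction two weeks later should count for less, yet its wording has that effect. A patient who tolerates injection 1 and reacts to injection 2 still satisfies both written conditions. The staff would then be following the protocol if they gave the shorter premedication and planned a 2-hour stay for someone already known to react.

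Injection reactions are a named risk, the drug has not been used in ME/CFS before, and safety and tolerability are the primary outcome. What is at stake is the care of an individual patient at the next dose.

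**Working it through.** The check is a reading of the rules side by side, followed by a count of injections. The protocol gives no figure of its own to reproduce.

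**1. Does the patient stay on the drug?** The stop rule (in the IRR section and again in Discontinuation of study intervention) can be read in two ways. The bracketed grade 4 may qualify both kinds of reaction or only the injection-related kind. Appendix 1 attaches the word severe to grade 3 ("Grade 3 (Severe): inability to work or perform normal daily activity"), so a grade 3 allergic reaction may also stop dosing. Under either reading a grade 1-2 reaction does not, and that is the usual grade reported for myeloma.

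**2. Is either condition tested again?** No. Both name the first injection only. The premedication rule covers all later injections. The observation rule covers injections 2 to 4.

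**3. Does anything else restore precautions?**

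| Provision | What it governs | Sets premedication or hours for the next dose? |
|---|---|---|
| Fitness check on the treatment day (schedules, footnote d) | Whether to inject | No |
| Physician assessment on arrival, injections 2-4 (Assessment during follow-up) | Whether to inject | No |
| Standard hospital procedure (IRR section) | Treatment of a reaction | Not as described; the procedure is not at hand |
| Investigator withdrawal for safety | Stopping | No |
| 4-6 weeks of observation after injection 2, first two patients | Delay; only going on to injections 3 and 4 depends on toxicity | No |
| At-least-2-hours wording (Efforts to reduce risks) | Minimum stay | Permits longer, does not require it |

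**4. How many injections are affected?** Let j be the injection at which the first non-stopping reaction occurs. Later injections on reduced premedication number 4 − j without maintenance and 7 − j with it. Injections still under the 2-hour rule number 4 − j, because that rule ends at injection 4.

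| j | Reduced premedication, no maintenance | Reduced premedication, maintenance | 2-hour rule |
|---|---|---|---|
| 2 | 2 | 5 | 2 (injections 3, 4) |
| 3 | 1 | 4 | 1 (injection 4) |
| 4 | 0 | 3 | 0 |
| 5 | – | 2 | 0 |
| 6 | – | 1 | 0 |

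**5. What is absent at each of these injections?** Treatment-day drugs: 5 − 3 = 2 (montelukast and intravenous dexchlorpheniramine). Dexamethasone: if the day 2-3 doses belong to injection 1 only, (10 + 4 + 4) − 10 = 8 mg. The text does not say whether they do. Observation: at least 6 hours against 2, a difference of about 4 hours.

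**6. Which injections have no stated observation period?** Three per maintenance patient, so at most 3 × 4 = 12. With 10 × 4 = 40 initial injections, that is 12 of at most 52 (23%). The premedication wording does reach these injections; the observation wording does not.

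These are counts of injections, not risks.

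**The case against.** The strongest reply is that clinical judgement is already required at every dose. Adverse events and fitness are assessed before each later injection, a physician sees the patient on arrival for injections 2 to 4, investigators may stop dosing, and the setting is an oncology clinic used to such drugs. Later first reactions are probably uncommon: the 9% refers to the first injection in myeloma, a lower risk is expected here, and the autoimmune series did not find reactions to be a clinical problem. The reduced regimen still includes dexamethasone, cetirizine and paracetamol at unchanged treatment-day doses. Longer stays are also hard on housebound or bedridden patients, in whom study procedures can themselves cause worsening (Possible risks). All of this stands and keeps the point small. It does not change what the written rule prescribes after a later reaction.

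A reader might infer more than the text supports:

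- *That staff are forbidden to observe for longer.* They are not. Efforts to reduce risks makes 2 hours a minimum.
- *That the first two patients' pause after injection 2 happens only if there is toxicity.* The four-to-six-week observation is unconditional. Only the next step is conditional: "If there is no serious, unexpected toxicity, we will proceed with another two injections two weeks apart".
- *That 2 hours replaces 6 at both injections 3 and 4 for any later reactor.* This holds only for a first reaction at injection 2.
- *That the protocol itself mandates the full regimen and a 6-hour stay after any reaction.* It says when the step-down applies and leaves the alternative unwritten. Continuing the first-injection regimen is a natural inference, not stated text.
- *That safety data are lost.* Nothing in the documents shows this.

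The missing observation period at weeks 26, 34 and 42 and the unwritten alternative regimen are omissions of detail. They would not carry a finding on their own.

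**Conclusion.** The point holds as a minor design fault. Both step-downs depend on injection 1 alone. A patient whose first non-stopping reaction comes at injection 2 or later is therefore assigned reduced premedication at up to 2 later injections, or up to 5 with maintenance. After a first reaction at injection 2 or 3, the 2-hour period, as a minimum, also runs through injection 4. Existing safeguards limit the risk but do not reset the rule.

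This rests on a literal reading of the two conditions and on grade 1-2 reactions not stopping dosing, which is true under either reading of the stop rule. The hospital's standard procedure could contain more than the protocol describes. The probability of a first reaction at a later injection cannot be derived from the documents and is probably low. No endpoint, estimate or test is affected.

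**What to change.** In Daratumumab intervention and in the IRR section, make the step-down conditional on no reaction to any earlier injection. A later first reaction would then be handled as a reaction to injection 1 would be: first-injection premedication and at least 6 hours' observation with intravenous access by default, with the physician able to decide otherwise after a grade 1 reaction. State whether the day 2-3 dexamethasone is part of that regimen. As an accompanying wording update, extend the observation period in the IRR section and in Efforts to reduce risks to weeks 26, 34 and 42.

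The change is to wording only and adds no new drug or procedure. The cost falls on patients who have reacted. Each later injection takes about 6 − 2 = 4 more clinic hours, intravenous access, montelukast 10 mg and dexchlorpheniramine 5 mg, plus 8 mg dexamethasone if days 2-3 are included. After a first reaction at injection 2 this comes to 4 × 2 = 8 hours and up to 8 × 2 = 16 mg over injections 3-4. With maintenance it is up to 4 × 5 = 20 hours and 8 × 5 = 40 mg over injections 3-7, if 2 hours would otherwise be used at injections 5-7. That is a real burden in this population and is the reason for the grade 1 exception.
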